**Table 1. Randomized Clinical Trials of Laparoscopy-Assisted Surgery for Rectal Cancer**

| Trial | Country | Trial registration | Tumor location              | Tumor stage | Chemoradiotherapy                           | The anticipated number of patients enrolled | Randomization ratio | Primary endpoint                                      | Secondary endpoint                                                        |
|--------------|----------------|---------------------------|------------------------------------|--------------------|----------------------------------------------------|----------------------------------------------------|----------------------------|--------------------------------------------------------------|----------------------------------------------------------------------------------|
| -            | China          | NCT00601549               | Below the peritoneal reflection    | Progressive stage  | Concurrent chemoradiotherapy                       | 600                                                | 1:1                        | Perioperative recovery indicators; oncological outcomes      | Recovery indicators at six months after the operation                            |
| -            | Spain          | NCT00782457               | Within 0-11 cm from the anal verge | T1-T3              | Capecitabine combined with radiotherapy (50-54 Gy) | 200                                                | 1:1                        | Perioperative recovery indicators; oncological outcomes      | Long-term efficacy                                                               |
| MRC CLASSIC  | Britain        | NCT00003354               | Colorectal                         | Unspecified        | Chemoradiotherapy                                  | 1200                                               | 2:1                        | 3-year local recurrence rate                                 | 3-, 5-, 7-year DFS rates and OS rates                                            |
| COLOR II     | Europe         | NCT00297791               | Within 15 cm from the anal verge   | T1-T3              | Undisclosed                                        | 1100                                               | 2:1                        | Local recurrence rate within three years after the operation | 3-, 5-, 7-year DFS rates and OS rates                                            |
| COREAN       | South Korea    | NCT00470951               | Within 9 cm from the anal verge    | Unspecified        | Chemoradiotherapy                                  | 340                                                | 1:1                        | 3-year DFS rate                                              | Quality of life (QoL) and anorectal function within one year after the operation |
| ACOSOG-Z6051 | USA, Canada    | NCT00726622               | Within 12 cm from the              | IIA, IIIA, IIIB    | 5-FU-based chemotherapy/radiot                     | 650                                                | Undisclosed                | Oncological outcomes                                         | disease-free survival and rate of local                                          |

|             |                                     |                         |                                                        |                       |                                          |     |     |                                                                                                                             |                                                  |
|-------------|-------------------------------------|-------------------------|--------------------------------------------------------|-----------------------|------------------------------------------|-----|-----|-----------------------------------------------------------------------------------------------------------------------------|--------------------------------------------------|
|             |                                     |                         | anal verge                                             |                       | herapy                                   |     |     |                                                                                                                             | recurrence, as well as
Quality of life(QoL)   |
| ALaCaR
T | Australi
a and
New
Zealand | ACTRN1260
9000663257 | T1-T3
rectal
cancer ≤15
cm from
anal verge | T1-
T3anyNany
M | 5-FU-based
chemotherapy/radiat
ion | 470 | 1:1 | Successful resection,
including complete
mesorectal excision
and negative
circumferential and
distal margins | Perioperative safety,
oncological
outcomes |

## **2. Objective**

To evaluate the perioperative safety and long-term efficacy of laparoscopy-assisted surgery for low rectal cancer compared to open surgery.

## **3. Participants**

Eligible participants are the patients who have an initial diagnosis of rectal cancer within 5 cm from the dentate line (by rigid proctoscopy). Clinical staging is determined by computed tomography (CT), endorectal ultrasound, and pelvic magnetic resonance imaging (MRI). No distant metastasis can be detected. No contraindication to general anesthesia. The participating patients have cT3/T4aN0M0 or cT1-4aN1-2M0 low rectal cancer without contraindications to preoperative radiotherapy or chemotherapy. Low rectal cancer is defined as a rectal adenocarcinoma with a lower margin within 5 cm from the dentate line as determined by rigid proctoscopy at diagnosis.

### **3.1 Inclusion criteria**

- 1) Aged 18-75 years;
- 2) Pathological diagnosis of rectal adenocarcinoma (including highly and moderately differentiated tubular adenocarcinoma, papillary adenocarcinoma, poorly differentiated tubular adenocarcinoma, mucinous adenocarcinoma, and signet-ring cell carcinoma);
- 3) The lower margin of the tumor is < 5 cm from the dentate line at the time of initial diagnosis by rigid proctoscopy;
- 4) cT1-3N0-2M0 or cT4aN0-2M0 adenocarcinoma after neoadjuvant chemoradiotherapy. Patients with pelvic lateral lymph nodes are ineligible;
- 5) Primary tumor < 6 cm in size;
- 6) No other concurrent primary cancers;
- 7) Adequate function of main organs, allowing surgical treatment;
- 8) Patients and their family members can understand the study plan, are willing to participate, and agree to give written informed consent.

### **3.2 Exclusion criteria**

- 1) Aged < 18 or > 75 years;
- 2) Concurrent or previous malignancies within five years;
- 3) Need for emergency surgery due to intestinal obstruction, intestinal perforation, intestinal hemorrhage, etc. ;
- 4) Previous history of colorectal surgery that might affect the reconstruction of the digestive tract;
- 5) Need to remove other organs in addition to the rectum;
- 6) ASA classification IV or V;

7) Current pregnancy or lactation:

- Women of childbearing age with a positive pregnancy test at baseline or who have not taken a pregnancy test; postmenopausal women must be at least 12 months postmenopausal;
- Sexually active men and women (of reproductive age) who are unwilling to take contraceptive measures during the study period;

8) Severe mental illness;

9) Inability to tolerate surgery due to severe emphysema, interstitial pneumonia, ischemic heart disease, etc.;

10) Continuous systemic steroid therapy within the last month;

11) Contraindications to laparoscopic surgery;

12) Patients and their family members cannot understand the conditions and objectives of this study.

## **4. Study design**

This study is a prospective, multicenter, randomized, open-label, parallel-group, noninferiority clinical trial.

## **5. Sample size estimation**

The sample size was estimated using a log-rank test based on a 3-year DFS with a noninferiority margin of 10%. At the time of this trial design, a noninferiority margin of 10% was determined to be clinically acceptable. Considering distinct prognoses in patients with stage I versus II/III disease, the sample size was calculated separately. Assumptions for 3-year DFS rate in the open surgery group were 94.3% and 75.2% for clinical stage I and II/III, respectively, 359 patients with stage I disease (laparoscopic 240, open 119), 609 patients with stage II/III disease (laparoscopic 406, open 203), and a total of 968 patients (laparoscopic 646, open 322) were required to provide an 80% power with a one-sided  $\alpha$  of 2.5%. One thousand sixty-five patients were aimed to enroll to allow for exclusions after randomization to maintain the required statistical power. All calculations allowed for a 20% dropout. The planned and follow-up period were three years and five years, respectively.

## **6. Intervention**

### **6.1 Preoperative chemoradiotherapy**

Patients with cT3/T4aN0M0 or cT1-4aN1-2M0 low rectal carcinoma undergo preoperative chemoradiotherapy before surgery and undergo surgery 6 to 8 weeks after completing the radiotherapy.

#### **6.1.1 Preoperative concurrent chemotherapy protocol**

According to the NCCN Guidelines (2013, v.4), for the treatment of rectal cancer, chemotherapy regimens based on 5-FU or its analogs are chosen. A regimen of capecitabine (825 mg/ m^2, twice a day, 5-7 days a week for five weeks) is recommended.

### **6.1.2 Preoperative radiotherapy protocol**

(1) Definition of target areas: The primary tumor and regional lymphatic drainage area's high-risk recurrence area must be irradiated. The high-risk recurrence areas of primary tumors include the tumor/tumor bed, the mesorectal region, and the presacral region. The target area for radiation treatment of carcinoma of the low rectum should include the ischiorectal fossa.

The regional lymphatic drainage areas include the lymphatic drainage area of the common iliac vessels in the true pelvis, the mesorectal region, the lymphatic drainage area of the internal iliac vessels, and the obturator lymph node area.

Radiation therapy techniques: According to the radiotherapy equipment available in the hospital, different techniques can be chosen, including conventional radiotherapy, three-dimensional (3D) conformal radiotherapy, intensity-modulated radiotherapy (IMRT), and image-guided radiotherapy.

CT simulation is recommended for radiotherapy treatment planning. If CT simulation is unavailable, conventional simulation must be performed. Patients should be placed in the prone or supine position with a full bladder.

Patients must receive irradiation in three or more fields.

If IMRT is necessary, the radiation treatment plan must be validated.

Local dose enhancement can be achieved through intraoperative or external irradiation.

Irradiation dose: The irradiation dose and schedule must be clearly defined regardless of which radiation therapy technology (conventional radiotherapy or new techniques, such as 3D conformal radiotherapy and IMRT) is used. The volumetric dose is defined for 3D conformal radiotherapy planning and IMRT, while the isocenter dose should be defined for conventional radiotherapy planning.

The protocol recommended for the high-risk recurrence area of the primary tumor and the regional lymphatic drainage area is a total dose (DT) of 45.0-50.4 Gy in 1.8-2.0 Gy per fraction for 25 or 28 fractions.

### **6.1.3 Preoperative chemotherapy during the interval between preoperative chemoradiotherapy and surgery**

As recommended by the academic advisory committee, an addition of preoperative capecitabine chemotherapy (1250 mg/ m^2, twice a day for 14 days) was performed between the end of radiotherapy and surgery.

## **6.2 Surgical treatment plan**

Surgery will be performed 6 to 8 weeks after the end of radiotherapy.

### **6.2.1 Open surgery**

This surgery includes standard TME and dissection of the No. 253 lymph nodes. The inferior mesenteric artery (IMA) is ligated either from its base directly or after the branching of the left colon artery. The rectum's distal resection margin (DRM) is at least 1-2 cm away from the tumor. The surgical method is chosen as follows:

(1) Transabdominal low anterior resection (LAR) or ultralow anterior resection (ULAR) may be chosen if the lower margin of the tumor is  $\geq 2$  cm from the proximal side of the anorectal ring.

(2) In cT1 and T2 patients, as well as T3 patients whose external anal sphincters are not invaded by the tumor (including patients who have undergone neoadjuvant therapy), intersphincteric resection (ISR) through either the transpelvic approach or transanal approach may be chosen when the lower margin of tumor is  $< 2$  cm from the proximal end of the anorectal ring.

(3) cT1 to T3 tumors that are  $\geq 5$  cm from the anal verge are confined to the intestinal wall within a depth of  $\leq 3$  cm and affect 1/2 of the circumferential wall of the rectum without invading the bladder, prostate, or vagina can be treated with ULAR via a pull-through procedure.

(4) Abdominoperineal resection (APR) can be performed in patients with external anal sphincter invasion.

(5) Extralevator abdominoperineal excision (ELAPE) can be performed via the pelvic approach in patients with levator ani muscle invasion.

For patients receiving sphincter preservation or partial sphincter preservation, loop transverse colostomy or ileostomy is recommended. See "9.6.1 Open surgery" for the detailed surgical procedure.

### **6.2.2 Laparoscopic surgery**

The indications of laparoscopic operation are the same as those of open operation. The operation follows the principle of TME and includes the dissection of the No. 253 lymph nodes. The IMA is ligated either from its base directly or after the branching of the left colon artery. The rectal DRM should be at least 1 to 2 cm away from the tumor. The principles for

selecting the intestinal segmental resection and/or reconstruction methods are the same as in **"6.2.1 Open surgery"**. Loop transverse colostomy or ileostomy is recommended for patients who undergo sphincter-preserving surgery. See **"9.6.2 Laparoscopic surgery"** for the detailed surgical procedure.

### **6.3 Adjuvant therapy**

Radiotherapy and chemotherapy are planned according to the postoperative pathological staging results. The details are presented in **"9.8 Adjuvant therapy"**.

## **7. Follow-up**

- Medical history is collected, and a physical examination is performed every three months for two years, then every six months for three years, and every year after five years.
- Carcinoembryonic antigen (CEA) and carbohydrate antigen 19-9 (CA19-9) are measured every three months for two years, then every six months for three years, and every year after five years.
- Abdominal/pelvic ultrasound and chest X-ray examinations are done every three months for two years, then every six months for three years, and every year after five years.
- An abdominal/pelvic MRI or non-contrast-enhanced plus contrast-enhanced CT scan is performed once a year. For patients who are allergic to contrast agents, non-contrast-enhanced CT alone is an alternative.
- Colonoscopy once a year; if a full preoperative colonoscopy could not be performed due to obstructing lesion, colonoscopy should be performed in 3-6 months after surgery
- Quality of life (QoL) is evaluated with the EORTC QLQ C30 and EORTC QLQ CR29 at three months, six months, and 12 months after surgery.
- Bladder function is assessed at five days, three months, six months, and 12 months after surgery.
- Sexual function is assessed at three months, six months, and 12 months after surgery.
- An anorectal function is assessed 12 months after surgery.
- Colonoscopy is performed within one year after surgery. Patients who show abnormal findings in the first examination must be examined again within one year. Patients who do not have polyps in the first examination will receive colonoscopy again three years and afterward once every five years. It is recommended to remove any colorectal adenomas found in follow-up examinations.

## **8. Study endpoints**

### **8.1 Primary outcome measure**

3-year DFS rate (final calculation is done 3 years after the last participant is enrolled)

### **8.2 Secondary outcome measures**

- Pathologic outcomes

Pathologic outcomes are defined as TME quality, negative CRM and negative DRM, length of proximal resection margin (PRM), length of DRM, and the number of retrieved lymph nodes.

- 30-day postoperative complications

- 30-day postoperative mortality

- 3-year and 5-year OS rates (calculated 3 and 5 years after the last participant is enrolled)

- Locoregional recurrence rate

### **8.3 Other pre-specified outcome measures**

- Operative outcomes:

- 1) Operation time (min)
- 2) Estimated blood loss (ml)
- 3) Conversion to open surgery (only applicable to the laparoscopic resection group)
- 4) Events of intraoperative complications

- Postoperative recovery outcomes

- 1) Time to first flatus (h)
- 2) Time to the first defecation (h)
- 3) Time to first liquid food (h)
- 4) Time to normal diet (h)
- 5) Duration of analgesic use (h)
- 6) Length of postoperative hospital stay (d)

- The Quality of life (QoL)

- 1) Quality of life (QoL) assessment: the EORTC QLQ C30 and EORTC QLQ CR29 scores

## 2) Bladder function assessment:

- The residual urine volume (1st measurement: after the urethral catheter is removed on the fifth day after the operation, the residual urine volume in the bladder is determined by B-ultrasound after the patient urinates as much as possible for the first time)
- I-PSS

## 3) Patient self-reported sexual function

Patient self-reported sexual function as assessed by the International Index of Erectile Function (IIEF-5) Female Sexual Function Index(FSFI) for male and female sexual function, respectively.

## 8.4 Definition of outcome measures

### 8.4.1 Disease-free survival (DFS)

DFS is defined as the period from the surgery date to the date of tumor recurrence or death (whichever comes first). In patients to whom this definition is not applicable, the last evaluation date is used for analysis. In addition, patients whose treatment is terminated without confirmation of tumor recurrence or metastasis should be followed up radiographically after the termination of treatment.

**The date of recurrence is defined as when obtaining a definitive diagnosis.**

**Tumor recurrence is diagnosed when any of the conditions below occurs:**

- Clear evidence showing tumor metastasis to the pelvis and pelvic lateral lymph nodes or inguinal lymph nodes
- Clear evidence showing metastatic lesions in the liver, lung, bone, etc.
- Death from any cause

**Note:** Without objective evidence (radiography/pathology), an increase in tumor markers alone or unexplained clinical deterioration does not necessarily indicate tumor recurrence.

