#### ■ 30-day postoperative complications

#### ■ 30-day postoperative mortality

#### ■ 3-year and 5-year OS rates (calculated 3 and 5 years after the last participant is enrolled)

#### ■ Locoregional recurrence rate

### **7.3 Other pre-specified outcome measures**

#### ■ Operative outcomes:

1) Operation time (min)

2) Estimated blood loss (ml)

3) Conversion to open surgery (only applicable to the laparoscopic resection group)

4) Events of intraoperative complications

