### 8.3.3 Outcome analysis

- **Analysis of primary outcome measures**

The DFS is calculated using the Kaplan-Meier method after the last participant has been enrolled for three years. The median DFS time and its 95% confidence interval are compared between the two groups using the log-rank test. Cox regression is used to calculate the hazard ratio and its one-sided 95% confidence interval between the two groups. According to the prespecified noninferiority criteria, the inferiority of the treatment to be tested compared with the control treatment is determined.

- **Analysis of secondary outcome and other pre-specified outcome measures**

(1) Pathologic outcomes, including the TME quality, negative CRM, and negative DRM, are presented as numbers (percentage) and compared using the Chi-square test.

(2) The operation time (min) and estimated blood loss (ml) are compared between the groups by the Wilcoxon method.

(3) The OS is calculated using the Kaplan-Meier method after the last participant has been enrolled for three years. The median OS time and its 95% confidence interval are compared between the two groups using the log-rank test.

(4) The OS when the last participant is enrolled for five years is determined by using the Kaplan-Meier method. The median OS time and its 95% confidence interval are compared between the two groups using the log-rank test.

(5) Time to tumor recurrence is determined using the Kaplan-Meier method. The median time of recurrence and its 95% confidence interval are compared between the two groups using the log-rank test.

(6) The perioperative recovery time is compared between the groups using the Wilcoxon method.

(7) The length of postoperative hospital stay (d) is compared between the groups using the Wilcoxon method.

(8) The incidence of intraoperative complications is compared between the groups by the  $\chi^2$  test or Fisher's exact probability method.

(9) After surgery, the incidence of complications and 30-day mortality rate are compared using the  $\chi^2$  test or the Fisher's exact tests for probability.

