**Table 12. Time to Tumor Recurrence (mon) (mITT)**

|                    | Laparoscopic Surgery Group | Open Surgery Group | P value |
|--------------------|-----------------------------------|---------------------------|-----------------------|
| N           | XXX                               | XXX                       | X.XXX                 |
| Censored(%) | XX(XX.X)                          | XX(XX.X)                  |                       |
| Events(%)   | XX(XX.X)                          | XX(XX.X)                  |                       |
| 25%(95%CI)  | XX.X (XX.X~XX.X)                  | XX.X (XX.X~XX.X)          |                       |
| 50%(95%CI)  | XX.X (XX.X~XX.X)                  | XX.X (XX.X~XX.X)          |                       |
| 75%(95%CI)  | XX.X (XX.X~XX.X)                  | XX.X (XX.X~XX.X)          |                       |

**Figure 5.** Kaplan–Meier curve for comparison of tumor recurrence rate between two groups (mITT)

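### The written recurrence definition includes death from any cause, so time to tumour recurrence has the same events as DFS, and locoregional recurrence has no definition, analysis or table

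*Combined protocol and SAP*

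**What the plan says.** Protocol 8.4.1 defines the primary endpoint: "DFS is defined as the period from the surgery date to the date of tumor recurrence or death (whichever comes first"). Directly below, under the same heading, it defines recurrence: "Tumor recurrence is diagnosed when any of the conditions below occurs". Three conditions follow:

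- a pelvic or nodal condition: "Clear evidence showing tumor metastasis to the pelvis and pelvic lateral lymph nodes or inguinal lymph nodes"
- a distant-site condition: "Clear evidence showing metastatic lesions in the liver, lung, bone, etc"
- a third condition that is not a tumour finding: "Death from any cause"

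A note adds that raised tumour markers or unexplained deterioration, without imaging or pathology, do not necessarily indicate recurrence.

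The secondary outcomes (protocol 8.2, SAP 7.2) include "Locoregional recurrence rate". Protocol 8.4, which defines the outcome measures, has no entry for it.

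For analysis, protocol 12.2 and SAP 8.3.3 item (5) state: "Time to tumor recurrence is determined using the Kaplan-Meier method", with a log-rank comparison. SAP Table 12 and Figure 5 report this separately from DFS (Tables 7 and 8, Figures 1 and 2). Neither document gives it an event definition, a time origin or a rule for death.

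**The concern.** Three things do not fit together.

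First, a death without cancer meets the written definition of recurrence. An analyst who follows the text will publish a recurrence curve that is really a recurrence-or-death curve. One who departs from it must decide without guidance how to treat deaths.

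Second, the recurrence outcome that the plan names is not the one that it analyses. Locoregional recurrence is the outcome in which a surgical approach to low rectal cancer would most plausibly show a difference, and no result for it is planned.

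Third, both tumour conditions are worded as metastasis, and the open-ended wording attaches only to the distant sites. The anastomosis, bowel wall and perineum are not named, although the operations in protocol 9.6 create an anastomosis or a perineal wound and protocol 6.1.2 treats the tumour bed as a high-risk area for recurrence. This item touches the primary endpoint. The trial is open-label, outcome assessment is by investigators at the centres (protocol 18.2), and no blinded review of recurrence is described. Whether such a failure counts would therefore be judged by people who know the arm.

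**Working it through.** **1. Event sets.** Let P be the pelvic or nodal condition, M the distant condition and D death from any cause.

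- Recurrence as written: R = P or M or D.
- DFS event: R or D = P or M or D, which is R.
- With death removed: R* = P or M. The DFS event is then R* or D = P or M or D, unchanged.

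Listing death therefore does nothing to DFS but makes time to recurrence identical to it in events. The two outputs need not match number for number: Table 7 is limited to 3 years after surgery, while Table 12 has no such limit and no stated origin. Protocol 8.4 offers two origins (surgery for DFS, randomisation for OS), so the origin cannot be inferred either.

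**2. Outcomes set against analyses.**

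| Item | Listed as an outcome (protocol 8.2–8.3, SAP 7.2–7.3) | Defined (protocol 8.4) | Analysed (SAP 8.3.3) | Table (SAP 9) |
|---|---|---|---|---|
| Locoregional recurrence | Yes | No | No | None of Tables 1–15 |
| Time to recurrence, any site | No | Only through the DFS list | Yes, item (5) | Table 12 |

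**3. Size of the mislabelling.** The plan states no event count, so I derive one from the sample-size section (protocol 5, SAP 8.1), taking the open-surgery DFS in both arms and no dropout.

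- Stage I: 359 × (1 − 0.943) = 20.5 events.
- Stage II/III: 609 × (1 − 0.752) = 151.0 events.
- Total: 171.5 events in 968 patients, or 17.7%.

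Assume that 10% to 25% of these are deaths without recurrence.

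- Deaths reported as recurrences: 0.10 × 171.5 = 17, to 0.25 × 171.5 = 43.
- Actual 3-year recurrence: 17.72% × 0.90 = 15.94%, or 17.72% × 0.75 = 13.29%.
- Overstatement: 17.72 − 15.94 = 1.8 points, to 17.72 − 13.29 = 4.4 points.

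**4. If deaths were censored instead.** With proportional cause-specific hazards, one minus Kaplan-Meier is 1 − (1 − 0.1772)^(1 − s), where s is the share of events that are deaths.

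- s = 0.10: 16.10% against 15.94%, about 0.2 points too high.
- s = 0.25: 13.61% against 13.29%, about 0.3 points too high.

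For any-site recurrence the choice of estimator matters much less than whether deaths are counted as events.

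**5. Unlisted sites: can an effect on noninferiority be derived?** Take stage II/III (406 laparoscopic, 203 open), a true deficit equal to the 10-point margin (75.2% against 65.2%) and one-sided 2.5%. If h points of one arm's failures go uncounted, that arm's observed DFS rises by h. By the normal approximation, the chance of declaring noninferiority is Φ(±h/SE − 1.96), with plus if the uncounted failures are laparoscopic and minus if they are open, and SE² = pL(1 − pL)/406 + pO(1 − pO)/203 at the observed rates.

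| h (assumed) | Uncounted in the laparoscopic arm | Uncounted in the open arm |
|---|---|---|
| 0 | 2.5% | 2.5% |
| 1 point | 4.5% | 1.3% |
| 2 points | 7.5% | 0.6% |
| 3 points | 12.0% | 0.3% |

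The documents give no site-specific rates by arm, so they fix neither h nor the column.

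**The case against.** The strongest reply is that this is a drafting slip. The list sits under the DFS heading, where repeating death is redundant but harmless. The DFS sentence names recurrence and death separately, and the SAP tabulates recurrence apart from DFS, so the authors plainly see them as different. That is fair as a reading of intent, and it settles the matter for DFS. It does not settle it for time to recurrence, for which no other definition exists.

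On the missing sites, the pelvis is listed first, and a recurrence at a low anastomosis can reasonably be read as pelvic disease. Appendix 2 requires every assessment confirming recurrence or new tumour to be entered in the eCRF. A patient with an unlisted first failure may later meet a listed condition or die, so some events would be late rather than lost. All of this stands. What remains is isolated anastomotic, luminal or perineal first failure, on a literal reading of the list.

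A reader might infer more: that DFS misses local failures in general, or that the omission favours noninferiority. The documents support neither. Pelvic failure is arguably covered, and the omission helps laparoscopy only if such failures are commoner after laparoscopy. The backgrounds of both documents cite meta-analyses finding no significant difference in local recurrence.

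**Conclusion.** Wrong as written for the secondary recurrence analysis, and it should be fixed. Two parts rest on the text alone: time to recurrence shares its event set with DFS, and locoregional recurrence is a named outcome with no definition, analysis or table.

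The 17 to 43 mislabelled deaths, and the overstatement of 1.8 to 4.4 points, depend on the assumed 10–25% share, equal arms and no dropout. They indicate scale and are not forecasts.

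The unlisted sites are an ambiguity in the primary event definition, with an effect of unknown size and direction. The table in step 5 should not be read as an estimate of bias, since each column assumes both a true 10-point deficit and where the uncounted failures fall. The fault lies in the definitions, not in data collection.

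**What to change.** - **Protocol 8.4.1:** remove death from the recurrence list and keep it as a DFS event only. State that anastomotic, luminal (bowel-wall) and perineal recurrence, confirmed by imaging or pathology, count as recurrence.
- **Protocol 8.4:** add a definition of locoregional recurrence that lists its sites, gives its time origin, and says whether a locoregional recurrence found after distant recurrence counts.
- **SAP 8.3.3 item (5), Table 12 and Figure 5:** add to or replace these with the 3-year cumulative incidence of locoregional recurrence by arm (Aalen-Johansen), with death without recurrence as a competing event, and the difference between arms with its 95% CI. If any-site time to recurrence is kept, give it its own event, origin and rule for death.

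The cost is definition text and one SAP analysis. No extra visits or procedures are needed, because assessments confirming recurrence are already to be recorded. Protocol 12 has the analysis plan finalised before database lock, so the change should be made by then.
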